### Participants

We will recruit two participant groups of equal size with differing diagnostic status: one group of individuals with clinically relevant depressive symptomatology and a control group of individuals without depression. The diagnostic groups will be matched according to gender and age. For the depression group, the main inclusion criterion is the presence of a diagnosis from the depressive spectrum according to ICD-10 criteria (F32 ‘depressive episode’, F33 ‘recurrent depressive disorder’, F34.1 ‘dysthymia’, and F43.20 & F43.21 ‘adjustment disorder with depressive symptoms’ [38]) according to the Structured Clinical Interview for DSM-5 Disorders - Clinician version (SCID-5-CV; German Version: [39]). The main inclusion criterion for the group without depression is a score < 10 on the Patient Health Questionnaire (PHQ)-8 [40]. Additional inclusion criteria for both groups include being ≥ 18 years, being able and willing to provide informed consent regarding study participation, and having sufficient German language skills (at least level B2 according to the Common European Framework of Reference for Languages). Exclusion criteria included the presence of any psychotic disorder (ICD-10 F2x), any substance dependence disorder other than nicotine (ICD-10 F1x.2), acute suicidality, any impairment of facial expression (e.g., due to facial paralysis or recent Botox treatment or autism spectrum disorder), and any type of dyschromatopsia. To ensure maximum external validity, we refrain from applying further potential exclusion criteria such as other clinical comorbidities, or concurrent pharmaco- or psychotherapy, but will record this information.

A power analysis was conducted with G*Power [41] to determine the necessary sample size for a 2-group-comparison of each of the intervention conditions (CR, CR + AFE, AFE) with the sham control condition. In absence of similar studies serving as reference for the determination of a critical effect, a team of three clinical experts agreed that an effect size of *d* = 0.5 would be therapeutically relevant. The power analysis yielded a necessary sample size of *n* = 32 for each of the four intervention conditions and two diagnostic groups based on a 2-sided analysis, a critical alpha-level of α = 0.05, and a power of β = 0.80. Hence, we will include *N* = 256 participants in total, composed in equal parts of participants with depression (*n* = 128) and without depression (*n* = 128).

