#### Efficacy of the reappraisal training augmented with facial expressions

In order to study the effectiveness of the EmpkinS-EKSpression app-based interventions, generalized linear models (GLMs) of the between-subject factors “diagnostic group” (with depression vs. without depression) and “intervention condition” (CR vs. CR + AFE vs. AFE vs. sham control), as well as the within-subject factor “time of assessment” will be applied in a stepwise fashion.

Regarding the primary outcome of depressed mood, we will first examine whether the mood induction phase *induces* depressed mood using a paired *t*-test with the pre- and post-mood-ratings as dependent variable (manipulation check). Further, hierarchical linear models (HLMs) will be implemented to assess whether the EmpkinS-EKSpression app-based interventions are effective in *reducing* depressed mood. As a first step, we will compare the CR condition with the sham control condition and the CR + AFE with the CR condition to study whether cognitive reappraisal training can be augmented with anti-depressive kinesthesia. As a second step, we will compare the AFE condition with the sham control condition. For continuously assessed secondary outcomes (i.e., positive mood, app data), corresponding analyses will be conducted.

With regard to secondary outcomes (i.e., GRID-HAMD, CES-D, current suicidality, ERSQ-ES, DAS-A, ATQ-R) assessed at pre-treatment, post-treatment, and/or follow-up, as well as pre/post mood-ratings, we will implement mixed analyses of variance (ANOVAs), again with the between-subject-factor, “study condition” (CR, CR + AFE, AFE, sham control) and the within-subject factor, “time.” Feasibility measures (treatment integrity, compliance, usability, acceptability) will be descriptively analyzed and contrasted between study conditions utilizing one-way ANOVAs. Finally, changes in kinesthesia and other psychophysiological measures over the course of the intervention, as well as differences between diagnostic groups and intervention conditions will be examined using, again, HLMs. All analyses will be conducted using the whole sample, as well as with the added between-subject-factor, “diagnostic group” (with vs. without depression). All analyses will be conducted with a significance level of α = 0.05. One-tailed tests will be used when the algebraic sign of the test statistic is specified; otherwise, two-tailed tests will be used.

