## Discussion

The aim of this study will be to evaluate the extent to which cognitive reappraisal in depression can be enhanced by deliberately performing anti-depressive facial expressions. Building on the ICS Theory of depression [12] and previous studies suggesting direct effects of manipulating kinesthesia (particularly facial expressions), on depressed mood [27, 28, 35], we assume that performing anti-depressive facial expressions during a cognitive reappraisal task will facilitate the invalidation of depressogenic cognitions and, hence, encourage a change in depressed mood. Should our hypothesis be confirmed, our findings would provide further evidence for the importance of the interaction of cognitive and implicational processes for the genesis of (sometimes clinically significant) affective states. Regarding clinical practice, findings from the present study could be used to further improve cognitive interventions for depression. Moreover, if the EmpkinS-EKSpression training demonstrates significant effects, it could be employed as a standalone or adjunct intervention for depression. Certainly, a more automated version of the app would greatly facilitate its dissemination, and so we will develop machine learning algorithms that enable automated facial expression recognition when these need to be coded before providing patients critical feedback. In the long term, our aim is to develop a fully-automated biofeedback training that outpatients can utilize solely with the aid of their smartphones, and to design the training flexibly enough that it can enhance in- or outpatient CBT, bridge treatment waiting times, and/or prevent relapses after successful CBT.

Further, the assessment of objective indicators of kinesthesia and the general body state of participants with and without depression (i.e., video data, psychophysiological measures, voice recordings), and the detection of patterns associated with depression using these indicators together with modern machine learning methods may have significant diagnostic implications. Automated detection of depression would open new ways to diagnose and monitor depression in a way that would not interfere with patients’ activities, and would be freed of biases that typically compromise the validity of self-report instruments [64].

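### The trial is sized two-sided at 0.05, but the analysis rule allows one-tailed tests at the same 0.05, which can reach the primary contrasts and double their false-benefit rate

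*Protocol article*

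**What the plan says.** The Participants section sizes the trial for a "2-group-comparison of each of the intervention conditions (CR, CR + AFE, AFE) with the sham control condition". It takes the view that "an effect size of *d* = 0.5 would be therapeutically relevant" and reports a calculation "based on a 2-sided analysis, a critical alpha-level of α = 0.05, and a power of β = 0.80". The result is 32 per condition within each diagnostic group, 256 in all.

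The section on efficacy of the augmented reappraisal training sets a significance level of 0.05 for every analysis and then states: "One-tailed tests will be used when the algebraic sign of the test statistic is specified; otherwise, two-tailed tests will be used". It does not lower the level for one-tailed tests.

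The same section asks, for the primary outcome, whether the app-based interventions reduce depressed mood. Hierarchical linear models (HLMs) are to compare CR with sham, CR + AFE with CR, and AFE with sham. The Discussion gives a direction for the augmentation question: "we assume that performing anti-depressive facial expressions during a cognitive reappraisal task will facilitate the invalidation of depressogenic cognitions".

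**The concern.** The two sections set different standards of evidence for the same comparisons. A two-sided 0.05 test allows a 2.5% chance of wrongly declaring benefit. A one-tailed 0.05 test in the favourable direction allows 5%. The primary contrasts have a sign and the question put to them is directional, so the one-tailed rule can govern them although they were sized two-sided.

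The practical effect is that a primary contrast favouring the intervention with a two-sided p-value between 0.05 and 0.10 could be reported as significant. A contrast tested only for benefit also cannot declare worsening. That matters most against sham: the active arms work through depressogenic statements in one training phase, while sham participants sort geometric forms.

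**Working it through.** **Inputs.** From the Participants section: d = 0.5 (standardised, so SD = 1), two-sided α = 0.05, power 0.80, 32 per condition and diagnostic group. From the analysis section: α = 0.05, with one tail when a sign is specified, and analyses on the whole sample as well as with diagnostic group as a factor. Pooling the diagnostic groups gives 32 + 32 = 64 per condition. The calculations use a two-sample t-test, as the article's sizing does, not the planned HLM.

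**Step 1: reproduce the plan's figure.** Power is the probability that a noncentral t variable with 2n − 2 degrees of freedom and noncentrality d√(n/2) passes the critical value.

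- Two-sided 0.05, power 0.80: n = 64 per condition, and 4 × 64 = 256. This matches the stated total when the diagnostic groups are pooled.
- One-tailed 0.05, power 0.80: n = 51 per condition, or 4 × 51 = 204.

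The stated total therefore matches the two-sided standard (or one-sided 0.025), not one-tailed 0.05.

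**Step 2: false claim of benefit per contrast.**

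- Two-sided 0.05: 0.05 / 2 = 0.025.
- One-tailed 0.05: 0.05, exactly double.

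**Step 3: smallest significant benefit at 64 per condition.** Formula: d_crit = t_crit × √(2/n), with 126 degrees of freedom and √(2/64) = 0.1768.

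- Two-sided: 1.979 × 0.1768 = 0.350.
- One-tailed: 1.657 × 0.1768 = 0.293.

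**Step 4: power at d = 0.5.**

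| Per arm | Two-sided 0.05 | One-tailed 0.05 |
|---|---|---|
| 64 (pooled, complete) | 0.80 | 0.88 |
| 32 (one diagnostic group) | 0.50 | 0.63 |

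The article states no dropout rate. If 5% to 15% were lost (an assumption; about 61 to 54 per arm), pooled two-sided power would be 0.78 to 0.73.

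**Step 5: worsening.** If the true effect were d = −0.5 with 64 per arm, the two-sided test would declare worsening with probability 0.80. The one-tailed test for benefit has no rejection region on that side.

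**The case against.** Much of the case on the other side is right, and it limits the point.

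- **Overall error.** A one-tailed test at 0.05 has a total type I error of 0.05, as the article says. Only the share in the favourable direction doubles. The rule is stated openly, and testing one-tailed after sizing two-sided raises power. This stands, and it is why the point concerns the evidence standard and not an inadequate sample.
- **Choosing tails afterwards.** A reader might infer that the number of tails can be picked once the results are known. The documents do not support that. The rule is tied to a sign that is specified, most naturally in the hypothesis. The article reports preregistration in August 2022, before recruitment began in January 2023. That record is not shown and may list the directional hypotheses. The absence of such a list from an article is no finding. Even a complete list would not remove the mismatch with the two-sided sizing.
- **Blindness to harm.** A reader might infer that the trial as a whole cannot see worsening. It can. Mixed ANOVAs are planned for GRID-HAMD, CES-D, suicidality and other secondary outcomes, and for pre/post mood ratings. Omnibus F tests across four conditions have no sign and respond to differences either way. The loss is confined to signed contrasts tested one-tailed.
- **Exposure to negative statements.** This does not separate CR from CR + AFE, which follow the same statement steps, and the mood inductions are identical in all arms. It bears only on the two sham contrasts, and only on the training trials.
- **Error over several contrasts.** A null simulation of the three contrasts gives about 13.5% for at least one false benefit one-tailed, against 7.0% two-sided. Those totals mix sidedness with the lack of a multiplicity adjustment, so they should not be charged to the one-tailed rule alone.
- **Reach of the Discussion quote.** It covers only the augmentation contrast. For the other two, the case rests on the analysis section's wording about reducing depressed mood, which makes one-tailed testing plausible but not certain.

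**Conclusion.** The point holds as an inconsistency between the sizing and the analysis rule. Wherever a sign counts as specified for a primary HLM contrast, the false-benefit rate is 5% instead of 2.5%, the significance threshold at 64 per arm moves from about d = 0.35 to d = 0.29, and that contrast cannot declare worsening.

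The doubling is exact and needs no distributional assumption beyond a symmetric test. The thresholds and power figures assume a simple two-group t-test on the pooled sample with all 64 per arm analysed; the planned HLM could shift them. The point is conditional on the one-tailed rule being applied to these contrasts, which the article permits but does not confirm. It should be fixed, but it does not threaten the viability of the trial.

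**What to change.** In the efficacy analysis section, replace the sentence on tails with one to this effect: all confirmatory between-condition contrasts are tested two-sided at 0.05 and reported with 95% confidence intervals; one-tailed testing at 0.05 is used, if at all, only for the mood-induction manipulation check. Using one-sided 0.025 would equally restore the false-benefit rate on which the trial was sized, though worsening would then have to be read from the two-sided interval.

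The cost is one sentence, with no added participants and no change in conduct. Power for the pooled comparison at d = 0.5 is 0.80, as the article already states, instead of 0.88. It is lower with dropout, and about 0.50 within a single diagnostic group, so the one-tailed rule does give up some power there. The change should be recorded before any results by condition are seen.

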#### Automated detection of depression

Machine learning methods will be implemented to examine the automated discrimination between individuals with and without depression based on kinesthesia and other psychophysiological data (i.e., facial expression and body posture from video data, facial muscle activity from EMG, respiration, heart rate (variability), and verbal acoustics from audio recordings). Initially, only video data (facial expression/body posture) will be used. Subsequently, psychophysiological data and verbal acoustics data will supplement the video dataset, providing additional modalities for analysis. Ultimately, our long-term goal is to adopt a multi-modal machine learning approach to leverage all data modalities available to enhance the accuracy and robustness of depression identification.

For the classification task (i.e., discrimination between individuals with and without depression), different machine learning pipelines will be trained. This will consist of different steps, from pre-processing and normalization to feature selection and actual classification. After the machine learning process, we will use explainable artificial intelligence techniques to identify discriminative features and to interpret the output of the machine learning models. To split the data into training and test sets, we will employ a standard train-test split using the scikit-lear library train_test_split function with a fixed random seed and allocating 80% of the dataset for model training and reserving 20% for evaluation. This approach ensures reliable performance estimation while guarding against overfitting. The performance of the classification models will be evaluated using established metrics such as sensitivity (i.e., $$\:\frac{number\:of\:true\:positives}{number\:of\:true\:positives+number\:of\:false\:negatives})$$ and specificity (i.e., $$\:\frac{number\:of\:true\:negatives}{number\:of\:true\:negatives+number\:of\:false\:positives}$$), which are indicative of the classification task’s performance with a benchmark of 80%. Furthermore, we will test whether the balanced accuracy (i.e., $$\:\frac{sensitivity\:+\:specificity}{2}$$) will exceed the null distribution.

Additionally, we will predict depressive symptom severity using machine learning-based regression models. The training of the models for the regression task will follow the same steps as for the classification task. As error metrics for the correspondence between clinical and machine-learning data, we will use Mean Absolute Error (MAE) and Root Mean Squared Error (RMSE). We will evaluate different machine learning models for both classification and regression tasks, such as k-Nearest Neighbour, Support Vector Machines, Decision Trees, Random Forests, and Artificial Neural Networks, to select the best-performing model based on predefined error metrics.

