#### Kinesthesia measures

For the analysis of (affective) facial expression, videos will be recorded using the built-in smartphone camera, which will be positioned in front of the participant at a distance of approximately 40 cm. A video for each emotion induction and training trial will be recorded, adding up to a total of 44 videos. In addition to these smartphone videos, two high-resolution RGB cameras (Sony SRG-300 H) will be used, one of them positioned directly in front of and the other to one side of the participant, both approximately 1.2 m away. Together, the cameras will record the participant’s face and upper body. We will extract information on facial expression (i.e., facial action units, eye gaze, head position, and facial emotions) from recordings of the front camera and information on body posture from the side camera. A third RGB camera will focus on the study therapist during the diagnostic session and training for adherence checks. Additionally, we will use an Azure Kinect depth camera (Microsoft, Redmond, WA, USA) to estimate participants’ body posture using the Azure Body Tracking SDK.

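### The single 20% hold-out for depression detection, about 26 people per class, is too small to support the claim of reliable performance estimation against the 80% benchmark

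*Protocol article*

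**What the plan says.** The section Automated detection of depression fixes one train-test split with a fixed random seed: "allocating 80% of the dataset for model training and reserving 20% for evaluation. This approach ensures reliable performance estimation". The same sentence goes on to claim protection against overfitting. Sensitivity and specificity are each set against a benchmark of 80%, and balanced accuracy is to be tested against a null distribution.

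The section then lists five model families as examples and says they will be compared "to select the best-performing model based on predefined error metrics". It does not say which data that choice uses.

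Two other sections bear on the point. Participants gives 256 people, 128 with and 128 without depression. Kinesthesia measures says of the smartphone recordings: "A video for each emotion induction and training trial will be recorded, adding up to a total of 44 videos". Further psychophysiological measures adds that EMG is recorded in all of the AFE condition and in a random half of the other three.

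**The concern.** Detecting depression from kinesthetic markers is one of the article's stated aims, and 80% is its only numerical yardstick for that aim. The plan makes a positive claim about its evaluation method, so this is not a matter of something left out. A fixed seed makes a split repeatable; it does not make the estimate precise. If the hold-out is small, a model clearly above the benchmark can miss it, a model below can reach it, and the report will not show which has happened because no interval is planned in the text. Choosing the winner on the same people would add an upward bias.

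**Working it through.** **Inputs.** N = 256, 128 per diagnostic group (Participants). 20% for evaluation, 80% benchmark, at least five candidate models (Automated detection of depression). EMG coverage (Further psychophysiological measures).

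**The plan's own N.** With d = 0.5, two-sided α = 0.05 and power 0.80, the normal approximation gives 2(1.960 + 0.842)²/0.5² = 62.8, so 63 per condition; the exact t calculation gives 64. Then 64 × 4 = 256, with the diagnostic groups pooled, which also equals the stated 32 × 8. N = 256 is therefore a sound base for the next step. It was sized for the intervention contrasts, not for a classifier.

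**Size of the hold-out.** 0.20 × 256 = 51.2, so 51 or 52 people, about 26 per class. No stratification is mentioned; a purely random draw of 52 would contain 20 to 32 people with depression (95% range, hypergeometric). EMG covers 64 + 0.5 × 192 = 160 people. If models with EMG use only those, the hold-out is 0.20 × 160 = 32, about 16 per class.

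**Precision (exact Clopper-Pearson, 95%).**

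| Observed | Proportion | Interval |
|---|---|---|
| 13/16 | 81% | 54% to 96% |
| 21/26 | 81% | 61% to 93% |
| 103/128 | 80% | 73% to 87% |

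The approximate half-width at 80% is 1.96 × √(0.16/26) = 15.4 points with 26 per class and 1.96 × √(0.16/128) = 6.9 points with 128.

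**Chance of meeting 80% on both measures, one model.** The smallest passing count is 21 of 26 (0.8 × 26 = 20.8) or 103 of 128 (0.8 × 128 = 102.4). The two classes are different people, so the binomial tail is squared.

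| True sensitivity = specificity | 26 per class | 128 per class |
|---|---|---|
| 75% | 0.337² = 0.11 | 0.090² = 0.008 |
| 85% | 0.815² = 0.66 | 0.936² = 0.88 |

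The column for 128 treats out-of-fold predictions as independent, which is an approximation.

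**If the winner is picked on the hold-out (conditional).** Five models, each truly at 75%, were simulated on 26 + 26 people, and the one with the highest balanced accuracy was kept. The correlation of their errors is not known, so it is assumed and varied.

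| Error correlation | Overstatement (points) | Winner meets 80% on both |
|---|---|---|
| 0 | 6.8 | 41% |
| 0.3 | 6.2 | 38% |
| 0.5 | 5.6 | 34% |
| 0.7 | 5.0 | 31% |
| 0.9 | 3.8 | 25% |

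The reported best balanced accuracy would thus average about 0.79 to 0.82 for models truly at 0.75, against an 11% pass rate for a single model.

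**The case against.** The best defence is that this is a condensed article. Tuning and model choice may be done by cross-validation inside the 80%, with the 20% touched once. The text is compatible with that: it reserves the 20% for evaluation and does not say where the choice is made. This stands. A reader might infer that the reported score is also the selection score, but the article does not establish it, so the optimism can only be stated conditionally. The imprecision remains either way.

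A reader might also infer, from 44 videos per person and a split of the dataset, that recordings of one person will fall on both sides. The article does not say so. The task is defined as discriminating between individuals, which makes the person the natural unit, and the count of 51 people used here assumes exactly that. The unit should be named, but no leakage is shown, and any figure for its size would depend on an assumed ratio of between-person to within-person variation.

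It would be tempting to note that a model truly at 80% passes both benchmarks only 33% of the time. That is weak evidence of noise, because the truth sits on the threshold: with 128 per class the figure is 0.500² = 25%. Models away from the threshold are the fair test. At a true 90%, the small hold-out passes 92% of the time, so the problem is greatest for models within roughly 5 to 10 points of the benchmark.

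Finally, the 80% carries no formal decision rule, the study is described as a proof of principle, and the primary outcome is not involved. That limits the importance but does not rescue the reliability sentence.

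**Conclusion.** The point holds for precision. By the article's own N and split, one hold-out of about 26 per class cannot deliver the reliability claimed for it: the interval around 81% spans 61% to 93%, a model truly at 85% misses the double benchmark about one time in three, and one truly at 75% meets it about one time in nine. This assumes a split by participant with roughly equal classes; the EMG figure further assumes that models with EMG use only the 160 people measured.

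The optimism is conditional on selection using the hold-out. Its size (about 4 to 7 points; a 25% to 41% pass rate at a true 75%) also rests on five equally good models and an assumed error correlation of 0 to 0.9. The planned test of balanced accuracy against a null distribution addresses only whether the model beats chance, not whether it reaches 80%.

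This should be changed, but it does not touch the randomised comparison.

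**What to change.** - Replace the single split by nested cross-validation, grouped by participant and stratified by diagnosis, over all participants who have the modality in question (256 for video, about 160 where EMG is required).
- Do feature selection, tuning and model choice in the inner loop only. This removes selection optimism whichever way the present text is read.
- Report out-of-fold sensitivity and specificity with 95% confidence intervals.
- For the balanced-accuracy test, permute the diagnostic labels and rerun the whole pipeline, including selection.
- Treat the 80% benchmark as descriptive. Requiring the lower confidence limit to exceed 80% would be a much stricter rule (112/128, or 87.5%, in each class) and is not proposed.
- Withdraw the sentence claiming reliable estimation and protection against overfitting.

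No data collection changes. The cost is computing time, some rewording and possibly a lower reported accuracy. The Trial status section gives recruitment as ongoing, so the change could be fixed before the models are run.

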**Methods:**

In a four-arm, parallel, single-blind, randomized controlled trial (RCT), we will randomize 128 individuals with depression and 128 matched controls without depression to one of four study conditions: (1) a cognitive reappraisal training (CR); (2) CR enhanced with instructions to display anti-depressive facial expressions (CR + AFE); (3) facial muscle training focusing on anti-depressive facial expressions (AFE); and (4) a sham control condition. One week after diagnostic assessment, a single intervention of 90–120-minute duration will be administered, with a subsequent follow-up two weeks later. Depressed mood will serve as primary outcome. Secondary outcomes will include current positive mood, symptoms of depression, current suicidality, dysfunctional attitudes, automatic thoughts, emotional state, kinesthesia (i.e., facial expression, facial muscle activity, body posture), psychophysiological measures (e.g., heart rate (variability), respiration rate (variability), verbal acoustics), as well as feasibility measures (i.e., treatment integrity, compliance, usability, acceptability). Outcomes will be analyzed with multiple methods, such as hierarchical and conventional linear models and machine learning.

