#### Further psychophysiological measures

EMG (bipolar) of the M. corrugator supercilii, M. zygomaticus major, M. orbicularis oculi, and M. masseter (the latter only in the AFE condition) will be assessed with the Biopac MP160 (Biopac Inc. Goleta, CA, USA) system. EMG measures will be assessed in a subsample (100% of the participants in the AFE condition and randomly chosen 50% of the participants in the other three conditions) to reduce participant burden. To assess kinesthesia markers potentially relevant to depression, also sensor-based physiological data will be recorded. We will use the Biopac MP160 system to record electrocardiogram (ECG) and respiration signals, from which we will extract heart rate (variability) (bipolar) and respiration rate (variability). In addition, we will use a novel, non-invasive radar-based technology positioned approximately 0.5 m behind participants to assess respiration and heart rate (variability). Here, for cross-validation purposes, we will employ two radar systems, a 24 GHz and a 61 GHz system. The radar-based technology has been shown to be a valid contactless measure of respiration and heart rate [60].

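### A single 20% hold-out, about 26 people per diagnostic class, does not give the reliable performance estimate the article claims for sensitivity and specificity near the 80% benchmark

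*Protocol article*

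**What the plan says.** The article's section on automated detection of depression (within the statistical analysis plan) describes classifiers that separate people with and without depression. On evaluation it states: "we will employ a standard train-test split using the scikit-lear library train_test_split function with a fixed random seed", "allocating 80% of the dataset for model training and reserving 20% for evaluation". The next sentence vouches for the method: "This approach ensures reliable performance estimation while guarding against overfitting".

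Sensitivity and specificity are then named as the metrics "which are indicative of the classification task’s performance with a benchmark of 80"%. As a further step, the section plans to test whether balanced accuracy "will exceed the null distribution".

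The sample available is given in the abstract: "we will randomize 128 individuals with depression and 128 matched controls without depression". EMG is recorded in only part of it. The section on further psychophysiological measures gives all of the AFE condition and a "randomly chosen 50% of the participants in the other three conditions".

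The article gives no size for the hold-out and no precision for either metric. Its power calculation, under Participants, concerns only the comparison of intervention conditions.

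**The concern.** Sensitivity is estimated only from the depressed people in the hold-out, and specificity only from the non-depressed. Each therefore rests on roughly a tenth of the sample. A fixed seed makes the split reproducible, but it does not make the estimate precise, because it only freezes one draw of test participants.

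Automated detection is a declared aim in the Background, and the Discussion attaches diagnostic implications to it. If the true performance lies near 80%, whether the detector is reported as reaching the benchmark depends heavily on who happens to fall into the test set. The article nevertheless tells the reader that the estimate is reliable. That is a stated property of the design, so it can be checked against the article's own numbers.

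**Working it through.** **Inputs.** From the article: 32 participants per condition and diagnostic group, four conditions, two diagnostic groups, a 20% hold-out, and an 80% benchmark for each metric. Assumed: the split is by participant (the article says only that the dataset is split), there is no dropout, and sensitivity and specificity errors are independent because they come from different people.

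**The article's sample size.** 32 × 4 × 2 = 256, or 128 per diagnostic class. This reproduces the stated total.

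**Hold-out size.** 0.20 × 256 = 51.2, rounded up to 52, so about 26 per class. If the split is not stratified, the number of depressed people among the 52 is hypergeometric (256, 128, 52), with SD 3.2 and a 95% range of 20 to 32.

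**Precision at 26 per class.** 20/26 = 76.9% misses the benchmark, so 21/26 = 80.8% is the smallest passing count. One person moves the estimate by 1/26 = 3.8 points. The normal 95% half-width at 80% is 1.96 × √(0.8 × 0.2 / 26) = 15.4 points. Exact (Clopper-Pearson) 95% intervals:

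| Result | Estimate | 95% interval |
|---|---|---|
| 21/26 | 80.8% | 60.6% to 93.4% |
| 24/26 | 92.3% | 74.9% to 99.1% |
| 25/26 | 96.2% | 80.4% to 99.9% |

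So 25/26 is needed before the lower limit clears 80%.

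**Chance of reaching the benchmark.** For one metric this is P(X ≥ 21), with X binomial (26, p). For both metrics at the same true value it is the square. The last column repeats this with 128 per class, where the smallest passing count is 103 (103/128 = 80.5%; 102/128 = 79.7% misses).

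| True value of each metric | One metric, n = 26 | Both, n = 26 per class | Both, n = 128 per class |
|---|---|---|---|
| 70% | 16% | 2.6% | below 0.1% |
| 75% | 34% | 11% | about 1% |
| 80% | 58% | 33% | 25% |
| 85% | 82% | 66% | 88% |
| 88% | 92% | 84% | 99% |
| 90% | 96% | 92% | above 99% |

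At a true 85% on both, the chance of missing at least one is 100% − 66% = 34%.

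**If every participant has an out-of-fold prediction.** 103/128 has an exact 95% interval of 72.5% to 86.9%. This interval and the last column treat out-of-fold predictions as independent, so they are somewhat optimistic.

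**The comparison with chance.** Under the null, the standard error of balanced accuracy is ½ × √(2 × 0.25 / 26) = 0.069. By normal approximation at one-sided 0.05, power is about 91% at a true balanced accuracy of 70% and above 99% at 80%.

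**EMG models.** There are 256 / 4 = 64 people per condition, so EMG is available in 64 + 0.5 × 192 = 160. For a model fitted only to people with EMG, the hold-out is 0.20 × 160 = 32, about 16 per class if the subsample is balanced by diagnosis. 13/16 (81.3%) then has an exact 95% interval of 54.4% to 96.0%.

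**The case against.** The strongest reply is that the weakness is local and the stakes are limited. Much of this stands.

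- **Clear cases are still recognised.** A reader might infer that the 80% benchmark cannot be judged at all, or that chance alone decides the result. The figures do not support that: a detector truly at 70% on both metrics passes both only 2.6% of the time, and one truly at 90% passes 92% of the time.
- **The 33% at a true 80% is not a fault of the sample size.** When the truth equals the benchmark, any design passes each metric about half the time, and with 128 per class the joint chance is 25%. The argument rests on the values either side of 80%.
- **Two criteria are not in conflict.** A reader might infer that beating chance is meant to count as meeting 80%. The article presents the test against the null distribution as an addition and makes no such equation. That test is adequately informative at this size.
- **The EMG figure is conditional.** Only EMG is subsampled. The article says psychophysiological data will supplement the video data and calls the full multi-modal approach a long-term goal. It does not say that everyone without EMG will be dropped.
- **Silence is not error.** Stratification and interval reporting are not mentioned, and a condensed article may leave them to a fuller plan. Nor does it say that the benchmark will be applied without intervals.
- **A locked hold-out is a legitimate design** where several model families compete. The claim that it guards against overfitting is not disputed here, provided model choice does not use the hold-out.
- **Weight.** Detection is separate from the randomised primary outcome, and the article ties no decision to the 80% figure.

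What remains is that the article itself chose the split and declared its performance estimate reliable. That claim does not follow at about 26 people per class for values near the benchmark. Treating the 44 videos per person as the unit would not rescue it: it adds no independent people and would place the same people in training and test.

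**Conclusion.** The reliability claim is wrong as written for sensitivity and specificity near the 80% benchmark. With about 26 people per class, a just-passing result is compatible with true values from about 61% to 93%, and true values of roughly 75% to 88% are poorly resolved. A detector at 75% on both metrics passes both 11% of the time, and one at 85% fails at least one 34% of the time.

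This rests on a participant-level split, no dropout (any loss shrinks the hold-out further), near-equal classes in the hold-out, and independence of the two metrics. It does not touch the efficacy analyses or the test against chance. The change should be made, because a declared aim is reported against this benchmark and the same data can estimate it more precisely.

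**What to change.** Replace the single hold-out with class-stratified k-fold cross-validation split by participant, and nest feature selection, tuning and model choice inside the training folds. Each participant then has one out-of-fold prediction per run; if runs are repeated, average over the repeats. Report sensitivity and specificity with 95% confidence intervals and interpret the 80% benchmark with those intervals. Delete or qualify the sentence that claims reliable performance estimation.

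If a locked hold-out is preferred, stratify it by diagnosis, report the interval, and remove the reliability claim. For any model restricted to people with EMG, state the number tested per class.

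The cost is plan wording and computing time, with no extra participants. Cross-validated intervals are approximate because the folds share training data.
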